#### Assessments and Blinding

Table 1 presents the trial measures and assessment time points. Assessments will occur at baseline (pretest), posttest, and 6 months after the program is completed. The trial will be triple blinded. Participants will be blinded as far as possible to the condition; they will only be informed that their workplace has been randomized to receive one of two programs: (1) an enhanced interactive mental health education program or (2) a standard written psychoeducation program. We will not provide participants with information about which program is expected to be the most effective. The statistician who will perform the analyses will be blinded to condition allocation (triple blind). Finally, assessments will also be blinded, as they rely on participants independently completing self-report measures on the web.

**Table 1 table1:** Assessment time points for the Helipad cluster randomized controlled trial of a brief workplace training program to support help-seeking for mental ill-health.

Construct	Measure	Presurvey	Postsurvey	6-month follow-up survey
Gender	What is your gender?	✓		
Age	What is your age?	✓		
Language spoken at home	What language do you usually speak at home?	✓		
Ethnicity	How would you describe your ethnicity?	✓		
Education	What is the highest level of education that you have completed?	✓		
Employment status	What is your current employment status?	✓		
Industry	What industry are you employed in?	✓		
Help-seeking intentions	GHSQ^a^	✓	✓	✓
Help-seeking attitudes	ATSPPH-SF^b^	✓	✓	✓
Help-seeking behavior: service use type and quantity	AHSQ^c^	✓		✓
Mental illness stigma	(SASS^d^-modified)	✓	✓	✓
Mental health literacy	D-Lit^e^ or A-Lit^f^ composite	✓	✓	✓
Depression symptoms	PROMIS^g^ Depression-Short Form	✓		✓
Anxiety symptoms	PROMIS Anxiety-Short Form	✓		✓
General psychological distress	DQ5^h^	✓		✓
Work and activity impairment	WPAI^i^	✓		✓
Quality of life	ReQoL-10^j^	✓		✓
Adverse events	Did you have any unexpected or negative experiences that might be related to completing this program?		✓	✓
Intervention acceptability	AIM^k^		✓	
Intervention appropriateness	IAM^l^		✓	
Intervention feasibility	FIM^m^		✓	
Debriefing	Explanation of study			✓
Interview	Interest in an interview		✓	

^a^GHSQ: General Help-Seeking Questionnaire.

^b^ATSPPH-SF: Attitudes Toward Seeking Professional Psychological Help Scale-short form.

^c^AHSQ: Actual Help-Seeking Questionnaire.

^d^SASS: Stigma and Self-Stigma Scales.

^e^D-Lit: Depression Literacy Questionnaire.

^f^A-Lit: Anxiety Literacy Questionnaire.

^g^PROMIS: Patient-Reported Outcomes Measurement Information System.

^h^DQ5: Distress Questionnaire-5.

^i^WPAI: Work Productivity and Activity Impairment.

^j^ReQoL-10: Recovering Quality of Life-10.

^k^AIM: Acceptability of Intervention Measure.

^l^IAM: Intervention Appropriateness Measure.

^m^FIM: Feasibility of Intervention Measure.

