**Methods:**

A 2-arm cluster randomized controlled trial will be conducted (target sample: N=900 from 30 to 36 workplaces, with n=25 to 35 participants per workplace). The trial will compare the relative effectiveness of an enhanced interactive program (intervention condition) with a standard psychoeducation-alone program (active control condition) on the primary outcome of professional help-seeking intentions as measured by the General Help-Seeking Questionnaire. Secondary outcomes include the impact on mental illness stigma; mental health literacy; help-seeking attitudes and behavior; work and activity functioning; quality of life; and symptoms of mental ill-health including depression, anxiety, and general psychological distress.

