#### Randomization

Given the cluster design, we will use a minimization approach to randomization [39]. Minimization is a type of randomization where the first participant (or cluster) is randomized and subsequent selections are allocated in a way that minimizes the imbalance on specific factors between groups. This method is helpful for a design with few participants (or clusters) and has the advantage of making each condition more closely matched on key factors across the trial. To implement this, we will use a preprogrammed computer algorithm that will assign each new workplace recruited into the trial into a condition. This process will aim to balance across conditions on the following key workplace characteristics: (1) workplace type (office-based vs non–office based), (2) organization size (<200 vs >200 employees), and (3) location (Australian Capital Territory or New South Wales or Victoria vs other Australian state or territory). Once a workplace has been allocated a condition, we will discuss with their key representative what participation in the trial involves and provide them with an email or SMS text message (depending on their preferred communication with employees) with an embedded link to their assigned study recruitment website. We expect the text to read as follows:

Would you like to participate in a research study testing a new resource for supporting employee wellbeing? Learn more about your mental health and wellbeing by completing a survey and a brief online program today: <link>.

We will ask the workplaces to send invitations to all their employees themselves, with each workplace determining who from within their organization will send this invitation. This process is designed to increase ecological validity, as the goal for the program is for it to be delivered by workplaces, we expect this to be a minimal burden (ie, 1 or 2 SMS text messages or emails) on the workplace administration staff tasked with sending invitations.

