#### Follow-Up Interview

In the follow-up survey, participants in the active intervention condition will be asked to indicate their willingness to be interviewed regarding their experience using the program by a member of the research team after the 6-month trial period ends. Interviews will explore experiences using the program and ideas to facilitate implementation. We expect that up to 15 interviews will be required to obtain a breadth of different experiences from participants from different workplaces, work levels (eg, management and employees), ages, and genders on their experiences and views on the co-designed program. Interview participants will be selected based on this diversity. The interview will be recorded on Zoom (Zoom Video Communications, Inc) or audio recorded over the telephone for accuracy, with the audio recording only stored on secure Australian National University (ANU) IT servers. The recordings will be transcribed for analysis by a professional external transcription company. Any references to the participants’ name or workplace will be removed in transcription to reduce the chance of identification in any publications. Consent for participating in interviews, recording of interviews, and using interview data for publication will be obtained separately for the trial. Participants will be emailed an Aus $50 (US $33) e-gift card to remunerate for their time and effort participating in an interview. Participants will receive an e-gift card if they commence the interview, regardless of whether they finish it or not.

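### The trial is called triple blinded, but the arm descriptions given to participants match the visible program format, so participants can identify their arm before rating the self-reported primary outcome

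*Protocol article*

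**What the plan says.** All of the blinding text is in Assessments and Blinding. It opens with the label "The trial will be triple blinded" and then covers three elements.

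- **Participants.** "Participants will be blinded as far as possible to the condition". They are told that their workplace was randomized to one of two programs: "1) an enhanced interactive mental health education program or (2) a standard written psychoeducation program". The section adds: "We will not provide participants with information about which program is expected to be the most effective".
- **Statistician.** The person running the analyses will not know the allocation.
- **Assessments.** The section says "assessments will also be blinded, as they rely on participants independently completing self-report measures on the web".

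The abstract uses nearly the same pair of terms for the trial's arms. It compares "an enhanced interactive program (intervention condition) with a standard psychoeducation-alone program (active control condition").

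**The concern.** The primary outcome is a self-rated intention to seek help, completed minutes after the program. Such a rating is open to expectancy: people who believe they received the better program may report stronger intentions, and people who believe they received the ordinary one may not. Blinding participants is the protection against this, and the article claims it.

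Two things are at stake. First, the final report would carry a blinding claim that the design does not support. Second, a difference in expectancy between the arms would enter the primary comparison as if it were a program effect. The trial is sized for a small effect (d = 0.2), so even a modest bias would matter, and recruiting more employees would not remove it.

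**Working it through.** **Step 1. Can participants identify their arm before the primary outcome?**

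| Question | What the protocol article says | Section |
|---|---|---|
| What are participants told? | Two possible programs, one enhanced and interactive, the other standard and written | Assessments and Blinding |
| What does the intervention look like? | Diagrams to click through, videos and quizzes; described as highly interactive | The Helipad Program |
| What does the control look like? | Written modules with minimal interactivity | Active Control Program |
| What is the order of events? | Baseline survey, then the program, then the posttest survey straight afterwards | Data Collection, Overview |
| What is rated at posttest? | GHSQ intentions, by self-report | Primary Outcome; Help-Seeking Intentions |

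The descriptions alone do not reveal the arm, because both are presented as possibilities. They do work as a key once the program is opened: interactive content matches one description and plain text matches the other. Recognition is therefore possible after the baseline GHSQ and before the posttest GHSQ. The estimand is the between-group difference in change from baseline to posttest. A shift that enters only at posttest passes straight into that contrast, and adjusting for baseline does not remove it.

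**Step 2. How many parties are blinded?**

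- Participants: able to identify their arm before the primary outcome, by Step 1.
- Assessors: the measures are self-completed, so the assessor is the participant. Assessment is exactly as blind as the participant and cannot count as a further blinded party.
- Statistician: stated to be blinded.

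One party is clearly blinded, not three.

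**Step 3. What could an expectancy shift do?** The article gives no figure for such a bias, so there is none to reproduce. The following is an illustration.

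Inputs from Power and Recruitment: at least 900 recruited, 25 to 35 per workplace, 15% attrition to posttest, intraclass correlation 0.02, two-sided 5% test. The 900 is taken as given, and the point does not depend on how it was derived. Assumed: true effect zero, a shift b of 0.05 or 0.10 SD in favour of the intervention, and no gain from baseline adjustment.

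Formulas, with N the number analysed and m the number analysed per workplace:

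- SE = sqrt((4/N) × [1 + (m − 1) × 0.02])
- False-positive rate = P(|Z + b/SE| > 1.96)

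| Recruited | N | m | Design effect | SE (SD units) | Rate, b = 0.05 | Rate, b = 0.10 |
|---|---|---|---|---|---|---|
| 36 × 25 = 900 | 765 | 21.25 | 1.405 | 0.0857 | 9.0% | 21.5% |
| 30 × 30 = 900 | 765 | 25.5 | 1.490 | 0.0883 | 8.7% | 20.5% |
| 26 × 35 = 910 | 773.5 | 29.75 | 1.575 | 0.0902 | 8.6% | 19.8% |

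First row in full: 900 × 0.85 = 765; 25 × 0.85 = 21.25; 1 + 20.25 × 0.02 = 1.405; sqrt(4 × 1.405/765) = 0.0857. For b = 0.10, b/SE = 1.167, and P(Z > 0.793) + P(Z < −3.127) = 0.214 + 0.001 = 0.215.

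The last row keeps the total near 900 at the largest cluster size, which takes 26 workplaces, fewer than the planned 30 to 36.

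Sensitivity: if baseline adjustment with an assumed pre-post correlation of 0.6 multiplies the SE by sqrt(1 − 0.36) = 0.8, the rates for the first two rows become about 11% (b = 0.05) and 29-31% (b = 0.10). A more precise analysis is more sensitive to a fixed bias.

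**The case against.** The strongest reply is that the protocol already qualifies participant blinding, withholds the expected result, and uses a time-matched active control, which itself limits expectancy effects. A visible behavioural program can rarely be fully masked. Recognition comes mainly from the format, which new labels cannot hide. Helipad also encourages help-seeking explicitly, so some demand effect would remain whatever the labels.

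Most of this stands, and it limits what relabelling can achieve. It does not rescue the triple-blind label or the claim about assessments. The qualifier covers what cannot be avoided, whereas the wording of the arm descriptions is a free choice.

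A reader might go further in five ways that the documents do not support:

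- *The descriptions are on the consent page.* That is plausible, but the article says only that participants are informed and does not say where.
- *Participants know which arm is expected to win.* They may infer it from the contrast between enhanced and standard. The article says it is not disclosed, and the abstract is not participant material.
- *The invitation unblinds control participants.* It reads "Would you like to participate in a research study testing a new resource for supporting employee wellbeing". One expected text is given, without distinction by arm, and the control program may also be new to employees.
- *The statistician is unblinded by the interview item.* Follow-Up Interview says "In the follow-up survey, participants in the active intervention condition will be asked to indicate their willingness to be interviewed". Nothing says this item reaches the analysis file. Table 1 also places interview interest in the postsurvey and shows no arm restriction, so the two places disagree on when it is asked.
- *The labels will bias the result by a known amount.* The documents give neither a size nor a direction, and the illustration cannot separate the labels from the visible format.

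**Conclusion.** The stated blinding is wrong as written. Participants can identify their arm on opening the program, before the self-rated posttest GHSQ, and a self-report by that participant is not a blinded assessment. This follows from the article's own sections and needs no assumption. At most, participants are not told the hypothesis, and the evaluative wording weakens even that.

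Whether bias follows, and how large it would be, is not known. On the assumptions shown (zero true effect, 900 recruited, no baseline adjustment), a shift of a quarter of the design effect (0.05 SD) would give a false-positive rate of about 9%, and a shift of half of it (0.10 SD) about 20-21%. These figures show how sensitive the primary comparison is; they do not predict bias. The correction changes no sample size, allocation, endpoint or analysis. It concerns participant wording and the accuracy of the blinding statement.

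**What to change.** 1. Describe both arms to participants in one neutral phrase, for example: one of two brief online programs about mental health and wellbeing. Drop the words enhanced and standard, and the interactive/written distinction that serves as the key to the arms.
2. In Assessments and Blinding, replace the triple-blind label with an accurate statement: the statistician is blinded to allocation; participants are not told the hypothesis but cannot be blinded to program format. Delete the claim that self-reported assessments are blinded, and use the same statement in later reports.

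Cost: slightly less descriptive participant information, a minor ethics amendment, and a less favourable blinding statement. Residual expectancy from the visible format will remain and should be acknowledged as a limitation.

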### Measures

#### Demographic Characteristics

These demographic characteristics are planned for assessment at preintervention: gender (male, female, nonbinary, different term, or other), age (18 to 25, 26 to 35, 36 to 45, 46 to 55, 56 to 65, or >66 years), ethnicity (open ended: “how would you describe your ethnicity”), language spoken at home (English only, English and another language, or another language only), level of education (primary school, some secondary school or year 10 equivalent, year 12, Certificate level I-IV, Diploma or Associate degree, Bachelor degree, Graduate Diploma or Graduate Certificate, Master degree, or Doctoral degree), employment status (eg, full time, part time or casual, unemployed, or not currently working due to studying or maternity leave), and work industry (business, consultancy, or management; accountancy, banking, or finance; charity and voluntary work; creative arts or design; energy and utilities; engineering or manufacturing; environment or agriculture; health or social care; hospitality or events; computing or Information Technology; law; law enforcement and security; leisure, sport, or tourism; marketing, advertising, or public relations; media or digital; property or construction; public services or administration; recruitment or human resources; retail or sales; science or pharmaceuticals; teacher training or education; and transport, logistics, or other).

#### Help-Seeking Intentions (Primary Outcome)

Help-seeking intentions will be measured by the intentions scale of the GHSQ [50]. The scale is an index, which for this study comprised 11 items measuring intentions to seek help “if you were having a personal or emotional” problem. Consistent with the GHSQ as a flexible index of help-seeking sources, we modified the scale to group nonprofessional informal sources together, that is, “partner, friend, parent, other relative/family member.” Furthermore, we added “Employee Assistance Programs,” and “internet-based treatment programs” to the potential sources of help and separated mental health professionals (ie, psychologists or counselors vs psychiatrists) to allow for economic analysis. Each source of help is rated on a 7-point Likert-type scale ranging from 1 (extremely unlikely) to 7 (extremely likely), with a midpoint at “unsure.” Item scores range from 1 to 7, with higher scores indicating greater intentions to seek help from that particular source.

#### Help-Seeking Attitudes

The help-seeking attitudes of participants will be measured using a 5-item updated version [51] of the Attitudes Toward Seeking Professional Psychological Help Scale-short form [43]. The 5 items retained were the positively-worded items of 1, 3, 5,6, and 7 and were selected based on factor loadings [52,53]. The scale asks respondents to indicate on a 4-point Likert-type scale (0=disagree and 3=agree) to what extent they agree with statements regarding psychological treatment (eg, “If I was having personal or emotional problems, the first thing I would do is seek professional help”). Scores are summed to produce a possible range of 0 to 15, with higher scores indicating more positive attitudes toward seeking professional help. Both the 5-item modified short form (Cronbach α=0.72) [52] and the 10-item scale have demonstrated sound psychometric properties [43,51,54].

#### Help-Seeking Behavior

Help-seeking behavior will be assessed by the proportion of participants reporting seeking help from a professional help-seeking source in the past 6 months on the Actual Help-Seeking Questionnaire [49]. This questionnaire consists of 10 items measuring self-reported help-seeking behavior. Participants are provided a list of help-seeking sources (matched to the abovementioned list for the intentions scale) and asked to indicate where, if any, they have “gone to for advice or help in the past 6 months for a mental health problem*.*” Furthermore, participants can indicate if they had seen someone else not listed, that they had not spoken with anyone about their problems, or that they had not experienced any problems. The number of visits to each health professional (psychologist or counselor, psychiatrist, family doctor or GP, and EAP) or the number of times a service was accessed (internet program and helpline) will also be assessed. Items from this scale specifying the number of contacts with each health professional or service will be used for the economic analysis.

#### Mental Health Literacy

Mental health literacy will be assessed using a bespoke measure generated by combining items from the D-Lit [41] and A-Lit [42]. The scale comprises 11 items (5 from the D-Lit questionnaire, 5 from the A-Lit, and 1 new item) that ask respondents to indicate their knowledge on a scale of true, false, or do not know for statements regarding the symptoms and treatment of depression and anxiety. Example items include “Depression does not affect your memory and concentration” (false) and “Generalized anxiety disorder is a common cause of workplace disability” (true). The new item added for this study was “Avoiding professional help for my mental health is unlikely to have an effect on my health long-term” (false). The original scales have good internal consistency and reliability, and scores on the bespoke measure will range from 0 to 11 (correct response=1 point), with higher scores indicating higher literacy [41,42].

#### Mental Illness Stigma

To measure stigma, we adapted the “stigma to others” scale from the Stigma and Self-Stigma Scales for attitudes toward mental health problems [40]. We generated a bespoke 4-item scale by retaining 4 of the 6 original items and slightly altering the wording (eg, changing mental disorder to “mental illness” for clarity and removing the word “suffering”). One item was removed due to a low factor loading of 0.32, and another item was double barreled and duplicated another item; therefore, we retained the item with the higher factor loading, leaving 4 items rated on a 5-point scale from 0=strongly disagree to 4=strongly agree: “Employees with a mental illness are less reliable than other employees,” “People with a mental illness are weak,” “People with a mental illness should just “snap out of it,” and “People with a mental illness are not really ill.” The original stigma to others scale demonstrated good validity and internal consistency (Cronbach α=0.71) [40]. Scores range from 0 to 16, with higher scores indicating higher stigmatizing attitudes toward mental illness.

#### Depression and Anxiety Symptoms

Depression and anxiety symptoms will be assessed using the PROMIS depression and anxiety [44] short form scales. They both comprise 8 items, each assessing the frequency of symptoms of depression or anxiety, respectively, during the past 7 days. The depression scale focuses on negative mood (eg, feeling unhappy), decrease in positive affect (eg, nothing to look forward to), and negative views of the self (eg, feeling helpless and worthless). The anxiety scale focuses on fear (eg, fearfulness), anxious misery (eg, worry), and hyperarousal (eg, tension and nervousness). Items are rated on a 5-point scale ranging from 1=never to 5=always, and the item scores are summed to produce an overall score ranging from 8 to 40, with higher scores indicating higher symptom severity. Both short forms correlate highly with the original scales (*r*=0.96) and demonstrate validity, with the depression scale correlating with the Center for Epidemiological Studies-Depression Scale (*r*=0.81) [44] and the anxiety scale correlating with the Mood and Anxiety Symptom Questionnaire (*r*=0.80) [44].

